##### Life satisfaction

Cantril’s ladder will be used to assess life satisfaction [38]. Participants are asked to rate their life satisfaction by placing themselves on a 10-step ladder, where the top represents the best possible life and the bottom the worst possible life. Cantril’s ladder has been shown to have good validity and reliability among adolescents [39].

##### Loneliness

The UCLA 3-item Loneliness scale will be used to assess participants subjective feelings of loneliness and perceived social isolation [40]. The original 20-item version of the scale has been found to be valid for assessment of loneliness among adolescents and young adults [41]. The 3-item version will be used as it has been found to be an adequate measure of loneliness when compared to the 20-item version [42].

##### Social connectedness

Social connectedness will be assessed using The Friendship Scale, a brief 6-item questionnaire originally developed to measure social isolation and perceived social support [43]. The scale has demonstrated good psychometric properties, including strong correlations with established measures such as the World Health Organization Quality of Life social relationships domain. A Danish translation of the scale has been validated in adults [44].

##### Symptoms of depression

The 13-item scale Mood and Feelings Questionnaire (Short Form) will be used to assess depressive symptoms [45]. Participants are asked to reflect on their experiences over the past two weeks. The Mood and Feelings Questionnaire has been found to be a valid measure of symptoms of depression in adolescents and young adults from the general population [46, 47].

##### Symptoms of anxiety

The Generalized Anxiety Disorder 2-item scale (GAD-2) will be employed to assess core symptoms of anxiety. The GAD-2 assesses symptoms of excessive worry and nervousness and is widely used for brief screening of generalized anxiety in the general population [48]. The GAD-7 has previously been used among young people aged 12–19 years, and GAD-2 consist of the first two items of the 7-item version of GAD [49].

##### Perceived stress

The 4-item version of Cohen’s Perceived Stress Scale measures the degree to which participants find their lives unpredictable, uncontrollable, and overloaded. Cohen’s Perceived Stress Scale is a widely used tool for assessing perceived stress, and the 4-item version has been found to have high internal consistency and reliability, and is significantly correlated with several criterion measures [50, 51].

##### Sleep quality

The 8-item PROMIS Pediatric Sleep Disturbance Short Form 8a will be used to assess sleep quality [52, 53]. It assesses adolescents’ experiences of sleep disturbances, including difficulties such as falling asleep and frequent awakenings. The questionnaire has demonstrated good content and construct validity among adolescents [52, 53].

##### Problematic smartphone use

The Smartphone addiction scale short version will be used to assess problematic smartphone use [54]. The Smartphone addiction scale short version consists of 10 items, assessing symptoms related to smartphone addiction such as daily-life disturbance, withdrawal, tolerance, and preoccupation. The scale has demonstrated excellent internal consistency and strong concurrent validity through significant correlations with related measures in adolescents [54].

#### Daily reports

To gain a more in-depth insight into participants’ habitual rhythm, emotional states, and social interactions throughout the study period, participants will receive a text message, where they will be reminded to complete the following 11 questions daily from baseline (day 1) to post intervention (day 42) (Supplementary Material 1). Six questions will ask them about their wake-up time and yesterday’s bedtime, school and/or work hours. Three questions will assess their current mood, perceived stress and sleepiness. Each item will be presented as a visual analogue scale (VAS), where participants place a marker along a continuum anchored by two descriptive words. VAS is chosen because it is quick to complete, impose minimal burden, and is sensitive to detecting small day-to-day fluctuations in emotional states and sleepiness. Prior research indicates that ecological momentary assessments with VAS can provide valid and reliable data on daily mood states in adolescents [55, 56]. The final two questions will assess if participants have had social interactions with individuals outside their household and who are not a part of their peer group. The 11 questions will be delivered via the SDU Connect application, which allows for momentary reporting in naturalistic settings.

#### Objective assessments

The following objective measures will be collected from day 1 until the post-intervention assessment (day 42), and some of the software-based assessments will continue to be collected until the long-term follow-up (day 70) (Fig. 2).

##### Physical activity, sleep, and stress

Participants will wear a Garmin Venu 4 watch capturing high resolution data from several sensors (e.g. accelerometry, thermometer, photoplethysmography) of circadian patterns of physical activity level and intensity, total sleep time and sleep stages, and heart rate variability. Garmin wearable devices with optical photoplethysmography have previously shown acceptable validity for several relevant outcomes, including selected measures of sleep, heart rate, and physical activity [57], and the validity of the specific device used in this trial will be evaluated separately in a dedicated validation study. The SDU Connect application will be used to synchronize data directly from the Garmin watch to a secure server at Avicenna Research using Garmin Health Software Developer Kit.

##### Social interactions

A bluetooth low energy (BLE) beacon (a small device that periodically transmits a unique identifier via BLE signals) will be attached to the Garmin Venu 4 watch. The SDU Connect application will scan the environment for 60 s every 5 min and record instances where participants from the same peer group’s BLE beacon are within a specified proximity range (approximately 5 m, Tx power − 20 dBm). Logging both the frequency and duration of these proximity events enables collection of time-stamped data on all social interactions between members of each peer group. This method has previously been used to track interaction between parent-adolescent dyads [58]. BLE beacons will also be set up in the participants own room and in the common room/living room of the participants home (if the participant is living together with other people e.g. family, friends, partner). This will enable objective tracking of time the participants spend in areas of the home where they are more likely to interact with other people.

In addition, we will track the geolocation of each participant’s smartphone in approximately 5-minute intervals via the SDU Connect application. Linking beacon proximity events with geolocation data will enable the identification of common locations and environments where each peer group typically meets at different times, thereby adding context to their social interactions. Moreover, it will be possible to assess the time participants spends outside of their home.

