### Conditions

#### Intervention

Participants in peer groups randomly allocated to the intervention will be instructed to reduce several forms of recreational screen media use over a4-week period that are hypothesized to affect mental health and related outcomes. These include high overall recreational screen media use, extensive smartphone use, social media use, solitary screen use, and screen behaviors that may interfere with sleep. Participants will therefore be asked to reduce their recreational screen media use across devices. For smartphone use, participants will be asked to reduce their use to a maximum of 1 h/day. Because social media use will not be permitted on computers or tablets during the intervention, this limit will also encompass participants’ social media use. Research staff will help each participant set up smartphone app limits for the ten most used social media and gaming applications, add a widget to their home screen showing the current amount of time they have spent on their phone, and finally turn off non-essential notifications. For television, computer and tablet use, participants will be asked to reduce their use to 14 h/week (with no specific daily limit), but social media use is not allowed on these devices. We will recommend participants to particularly reduce their solitary screen media use and prioritize co-viewing activities and socially connected gaming with peers and family members during the intervention. Participants will be asked to keep their devices outside the bedroom. To support this, they will be provided with a free alarm clock, as many people use their smartphone to set alarms (see Table 1 for an overview of the intervention components).

**Table 1 Tab1:** Screen media reduction intervention

	Intervention components
Smartphone use	• Maximum of 1 h/day • Add a widget to their home screen displaying daily smartphone use • Set up smartphone app limits on most used apps (social media and games) • Turn off non-essential smartphone notifications (essential include: calls and text messages)
Television, computer, and tablet use	• Maximum of 14 h/week • No social media use is allowed on these devices and participants are recommended to reduce their solitary screen media use and prioritize co-viewing activities and socially connected gaming with peers and family members
Screen media use and sleep routines	• Leave screen media devices outside the bedroom • Free alarm clock

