##### Screen media use

Screen media use will be tracked using three different methods. The SDU Connect application will be used to track smartphone and tablet use (overall screen time, time spent on specific applications, phone log, message log, and notification log) from Android and iOS devices. Computer use will be tracked using Manictime software (FinKit, Slovenia). Manictime data (overall computer usage and time spent on specific applications (e.g. Microsoft Word, Google Chrome) and websites (e.g. www.youtube.com, www.netflix.com) will be stored directly on a local server at the University of Southern Denmark. An in-house developed TV monitor will be used to track TV use on participants’ own TVs and any shared TVs in the household if any [59]. TV monitors will be equipped with a BLE beacon tracking when the participant is close to the TV (approximately 5 m, Tx power − 20 dBm). Combining use data from the TV monitor with BLE beacon data enables construction of time series datasets showing when the TV is on and a participant is nearby - indicating that they are likely watching.

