##### Key confirmatory secondary outcomes

The following four key secondary endpoints are specified a priori to support mechanistic interpretation by quantifying behavioral changes plausibly linking reduced screen media use to changes in mental wellbeing:

Face-to-face social interaction with peers (objective, Bluetooth beacons).

The primary peer-interaction metric will be total time spent in proximity-events with peer-group members (minutes/week) based on BLE beacon data collected via the SDU Connect application, which logs frequency and duration of proximity events within a predefined distance threshold. The exact aggregation will be prespecified in the statistical analysis plan.

Face-to-face social interaction with other people (daily self-report).

Self-reported daily social interactions with people who are not a part of the peer group or the participants’ household (e.g. family members not living in the household, other friends, other relations). The exact aggregation of the self-reported interaction data will be prespecified in the statistical analysis plan.

Total sleep time (objective, Garmin).

Total sleep time derived from continuous monitoring using Garmin Venu 4, as per device algorithms for total sleep time.

Physical activity (objective, Garmin).

Physical activity derived from continuous monitoring using Garmin Venu 4. The exact algorithm for processing raw Garmin data will be prespecified in the statistical analysis plan.

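### Room, location and peer-proximity measures depend on where the smartphone is, and only the intervention arm is asked to change where it is kept, so arm-dependent error is likely

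*Protocol article*

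**What the plan says.** The Social interactions section describes a beacon as a small device that sends out an identifier at intervals. One such beacon "will be attached to the Garmin Venu 4 watch". Detection is the app's task: "The SDU Connect application will scan the environment", for one minute in every five, recording when beacons of the same peer group are within about 5 m. In the home, "BLE beacons will also be set up in the participants own room and in the common room/living room of the participants home", and this is read as time the participant spends in those parts of the home. Geolocation is explicitly that of the participant's smartphone, and is read as time outside the home. The same section presents the proximity log as covering every interaction between peer-group members.

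Under Screen media use, "The SDU Connect application will be used to track smartphone and tablet use", which places the app on those devices. For television, "TV monitors will be equipped with a BLE beacon tracking when the participant is close to the TV"; the receiver is not named there.

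Under Intervention, smartphone use is capped at 1 h/day and "Participants will be asked to keep their devices outside the bedroom". Under Control, participants are asked to leave their use of devices unchanged.

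Key confirmatory secondary outcomes defines the peer metric as "total time spent in proximity-events with peer-group members (minutes/week) based on BLE beacon data collected via the SDU Connect application" and leaves the exact aggregation to the SAP. Anticipated limitations mentions evasion through untracked devices, and points to the objective measures as the counterweight to unblinded self-report.

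**The concern.** A sensor that follows the phone stands in for the person only while the two are together. The intervention acts on that link directly through the bedroom rule, and perhaps indirectly through the use cap. The control condition does not. Because the change begins at randomization, the 14-day baseline cannot adjust it away. An apparent move from bedroom to shared space could arise without anyone moving, and a real gain in time with peers could be partly hidden. These are among the measures the article relies on to offset bias in self-report.

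**Working it through.** The documents give no figure on this point to reproduce, and no phone-carriage rates. The check traces each measure and then illustrates the size under stated assumptions.

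**Trace.**

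| Measure | Transmitter | Receiver | What is recorded | How it is read |
|---|---|---|---|---|
| Peer proximity | Beacon on the peer's watch | App | Phone to peer's wrist | Contact between two people |
| Own-room / common-room time | Fixed beacon | App | Phone to room | Participant in that room |
| Geolocation | none | Smartphone | Phone location | Participant at home or out |
| TV proximity | Beacon on TV monitor | Not stated | Phone to TV, if the app is the receiver | Participant near the TV |

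The watch is nowhere described as a scanner. For fixed beacons the app as receiver follows from the article's own description of a beacon and of the app's scan.

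**Room time.** Assumption: 8 h per night in the bedroom, with the phone in the common room on a share *a* of nights. Misplaced hours per week = 8 × 7 × *a*.
- *a* = 1: 56 h/week, the upper bound
- *a* = 0.25: 14 h/week

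These hours leave own-room time and are counted as common-room time, with no change in where the person is.

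**Peer proximity, two members together.** Let *c* be the share of contact time in which a member's phone is with its owner, independently between members. Assumption: *c* = 0.95 in controls and 0.90, 0.80 or 0.70 in the intervention arm.
- One phone's log only: relative error = c_int / c_ctl − 1
- Either phone may log: relative error = [1 − (1 − c_int)²] / [1 − (1 − c_ctl)²] − 1, with control detection 1 − 0.05² = 0.9975

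| c_int | One phone | Either phone |
|---|---|---|
| 0.90 | 0.90/0.95 − 1 = −5.3% | 0.99/0.9975 − 1 = −0.8% |
| 0.80 | 0.80/0.95 − 1 = −15.8% | 0.96/0.9975 − 1 = −3.8% |
| 0.70 | 0.70/0.95 − 1 = −26.3% | 0.91/0.9975 − 1 = −8.8% |

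At the worst row, a true +20% would appear as 1.2 × 0.912 − 1 = +9.5% (either phone) or 1.2 × 0.737 − 1 = −11.6% (one phone). With equal carriage in both arms the relative error is zero.

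**Three members together** (the mean group size under Sample size calculations). If a participant is credited whenever any of the three phones is present, detection is 1 − (1 − c)³. The error is then −0.1%, −0.8% and −2.7% for the same three rates. Phones left together in another room break the independence assumption and would make both the dyad and the trio figures worse.

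**The case against.** Much can be said for the plan. A limit on use is not a limit on carrying: calls and text messages stay among the essential notifications, and nothing tells participants to leave the phone behind when they meet friends. The only placement instruction is the bedroom rule, listed with sleep routines. Any member's phone can log a contact, which dampens the loss. Room time and time outside the home are neither primary nor key secondary outcomes, and watch sleep data with daily bed and wake times would allow night hours to be masked. Crediting and missing-data rules are SAP content, which the article openly defers. It also condenses a full protocol that may hold the app's settings.

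Most of this stands, and it limits the point. Three stronger readings might be inferred and are not supported:
- That the peer endpoint is shown to be biased downward by up to 26%. That figure needs assumed carriage rates and a one-way derivation that the article does not adopt.
- That TV time is under-recorded and compliance therefore flattered. The TV receiver is not named. If it is the phone, a handset parked by the TV errs one way and one left elsewhere errs the other.
- That the objective measures as a whole are compromised. Sleep and physical activity come from the watch.

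What the objection does not answer is data capture. Aggregation rules cannot recover a contact that no phone recorded, nor show afterwards whether the phone was with its owner. The article allows the SAP to be finalized until shortly before the last group finishes, which is too late to add a signal to the scans.

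**Conclusion.** The concern holds as a should-fix. Reading phone-based signals as the participant's position is likely to introduce error that differs by arm, and the limitations section does not acknowledge it.

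- **Own-room and common-room time:** the clearest case. If the bedroom rule is followed, the phone cannot show that its owner is in the bedroom (apart from a phone close enough outside to be misread as inside). The shift is 14 to 56 h/week under the 8 h and common-room assumptions, in a direction that can mimic more time in shared space.
- **Peer proximity time:** the one key secondary endpoint exposed. The likely error is under-detection in the intervention arm, against the hypothesis. Its size is unknown; the range worked above rests wholly on assumed carriage rates.
- **Time outside the home:** may be under-recorded if phones are left behind, which is plausible but not instructed.
- **TV proximity:** may be misclassified in either direction, if the phone is the receiver.

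The primary outcome (WEMWBS), watch-based sleep and physical activity, and self-reported contact outside the peer group do not depend on phone position.

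**What to change.** At data capture, before more groups are enrolled: if it is not already done, have the app log each participant's own watch beacon in every scan, as a check that phone and owner are together.

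In the derivation rules:
- Treat room and location epochs without own-beacon detection as missing, not as absence.
- Credit a peer contact if any member's phone detects it.
- Exclude night-time or sleep hours from the room-beacon measures in both arms.
- Report the share of valid epochs by arm and period, with a sensitivity analysis for differential carriage.

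In the text: qualify the claim under Social interactions that every interaction between members is captured, and qualify the reliance on objective measures under Anticipated limitations. State which device receives the TV beacon.

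The cost is one more beacon identifier in the scan list and a few derivation rules. Some epochs will be discarded, and a phone within about 5 m but in the next room will still be misread.

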##### Screen media use

Screen media use will be tracked using three different methods. The SDU Connect application will be used to track smartphone and tablet use (overall screen time, time spent on specific applications, phone log, message log, and notification log) from Android and iOS devices. Computer use will be tracked using Manictime software (FinKit, Slovenia). Manictime data (overall computer usage and time spent on specific applications (e.g. Microsoft Word, Google Chrome) and websites (e.g. www.youtube.com, www.netflix.com) will be stored directly on a local server at the University of Southern Denmark. An in-house developed TV monitor will be used to track TV use on participants’ own TVs and any shared TVs in the household if any [59]. TV monitors will be equipped with a BLE beacon tracking when the participant is close to the TV (approximately 5 m, Tx power − 20 dBm). Combining use data from the TV monitor with BLE beacon data enables construction of time series datasets showing when the TV is on and a participant is nearby - indicating that they are likely watching.

#### Evaluation of the intervention

##### Questionnaire

Participants in the intervention group will complete a post-intervention questionnaire assessing their experiences with the 4-week screen media reduction. The questionnaire includes brief closed-ended and open-ended items designed to evaluate overall acceptability, perceived difficulty, and experienced impact of the intervention components (Supplementary Material 2).

##### Interview

The aim of the qualitative data collection is to explore how participants interpret and reflect on the screen media reduction, and how they perceive its influence, e.g. on their social lives and well-being. This will also include attention to unintended intervention outcomes [60]. By illuminating participants’ meaning-making processes, this component will provide a deeper understanding of the study’s quantitative findings.

A subsample of the participants in the intervention group will be invited to participate in individual or focus-group interviews. Participants will be selected through purposive sampling and diversity within and across peer-groups, including variation in characteristics such as age and sex. Guided by the concept of information power [61], the aim is not to maximize sample size, but to generate rich, contextually grounded data and well-substantiated interpretations.

The interviews will preferably be conducted in person at the university or another place preferred by the participant. We will strive to create a safe and trusting environment. We use an interview guide with concrete and open-ended questions, employing creative prompts, and engaging in reflexive listening [62]. This approach is designed to ensure that young participants feel safe and comfortable during the interviews, while also securing the depth and quality of the data generated.

Prior to interviews, additional oral information will be provided. Participation in the interviews is voluntary; participants may skip questions, withdraw at any time, or choose not to elaborate. They will be reminded that there are no “right” or “wrong” responses. Sensitive topics may arise, in which case the interviewer will pause and, if needed, provide information on support services.

